#### Financial Incentives

To encourage retention and initial goal attainment, participants will earn the following financial incentives for successfully completing each phase of the trial: Screening - $20; Lab 1- $20; Baseline week 1 - $20; Baseline week 2 - $20; Prescription - $175; Follow up 1 - $50; Follow up 2 - $30; Follow up 3 - $35; Follow up 4 - $40; Follow up 5 - $45; Follow up 6 - $50; Follow up 7 - $55; Follow up 8 - $80; Full compliance bonus - $50, yielding maximum total payment of $730. All financial incentives will be offered solely for completing assessments, except for the prescription phase incentive, which requires also meeting behavioral targets, and the bonus payment, which requires completing all assessments on time. Payment will be cumulated over the course of study participation and paid out at termination when the participant returns the PDA.

### Assessment Instruments

#### Screening

MBC's web-based dietary screening questionnaire will be the 27-item Rapid Food Screener [27], a food frequency questionnaire that estimates daily fruit/vegetable servings, total fat, saturated fat, and percent total and saturated fat. The web-based activity screener will be the Physical Activity Recall Questionnaire (PAR) [21], an 8-item questionnaire that assesses moderate-vigorous activity for the past 7 days and past month. Because no validated screening measure was available for sedentary screen time, we created a parallel 5-item questionnaire to assess time devoted to targeted sedentary activities over the same period as the PAR. Current substance abuse, eating disorders, and suicidality will be evaluated by the Structured Clinical Interview for DSM-IV Diagnosis--Non-Patient Version (SCID-NP) [28] and the Hamilton Rating Scale for Depression [29] during the in-person screening visit.

#### Descriptive

Demographic information, anthropometric data, motivation and readiness for health behavior change, and past history of dieting and exercise will be assessed during screening. Demographic data to be gathered are: gender, age, ethnicity, marital status, education, income, and household size. Weight and height will be measured using a balance-beam scale to the nearest 1 lb and .1 in, respectively. Body Mass Index (BMI) will be calculated as (weight in pounds/(height in inches) 2) × 704.5, the mathematical equivalent of the BMI metric calculation (kg/m2). Waist and hip circumference will be assessed using a tape measure, to the nearest .1 in.

Reasons for enrolling in the study will be measured by a modified Motivation for Physical Activities scale [30]. Items have been altered to ask about eating as well as activity changes. Seven questions about financial motivation to participate have been added, and the social scale has been deleted (as not applicable). The resulting 32-item Motivation for Health Behavior Change in an Experimental Setting questionnaire yields five motive subscales (fitness, appearance, competence/challenge, enjoyment, and financial incentives). To assess prior dieting experience, participants will complete a four-item Diet Familiarity Scale adapted from Project EAT [31]. The Familiarity Scale asks about previous experience with each prescribed eating and activity change. To examine the influence of response bias on diet and activity self-reports, the degree of felt need to present oneself in a favorable light will be assessed during screening by the 33-item Marlow-Crowne Social Desirability Scale [32].

Activity Liking and Craving Questionnaires will be administered during screening as an aid for coaching and a means to identify preferred foods and activities to be offered during recreational laboratory sessions. The questionnaires assess self-reported preference and urge to consume specific FV, high saturated fat foods, physical activity, and sedentary leisure activities. Each questionnaire presents familiar items that participants rate using Rozin et al's (1991) [33] 9-point hedonic scale. Participants will complete the questionnaires once to express food and activity liking, where response options range from 1 = dislike extremely to 9 = like extremely. Then, without access to their liking ratings, they will re-rate the items to report craving. Anchors for the 9-point craving scale will range from 1 = little or no urge to 9 = extreme urge. The Food Liking and Craving Questionnaire presents 10 sweet foods high in saturated fat, 10 savory foods high in saturated fat, 10 vegetables, and 10 fruits. The Activity Liking and Craving Questionnaire presents 10 moderate/vigorous intensity athletic activities, 10 moderate intensity work or household activities, 10 sedentary work or home-related activities, and 10 sedentary recreational activities including the ones targeted for change in this study. Coaches will use these measures to identify low rate but liked FV and activities to suggest to participants. Participants' responses will also be used to select four fruits/vegetables and four physical activities with liking ratings of approximately 5 and four high saturated foods and four sedentary pastimes with ratings of approximately 7. Those items will be offered for purchase in the Want Task and made available in the recreational laboratory. Participants will rate their liking for the eight chosen reinforcers prior to each recreational laboratory session in order to verify that the options offered are experienced as pleasurable.

#### Psychological and Behavioral Process Measures

To identify psychological processes that accompany (and potentially mediate) behavior change, a series of measures will be administered towards the end of the baseline and prescription periods. Readiness and self-efficacy to make behavioral changes will be assessed during baseline and prescription periods. Readiness to change physical activity will be evaluated by Physical Activity Staging (PAS) [34]. Readiness to change sedentary leisure will be measured by a parallel PAS Sedentary Behavior Staging Questionnaire. Dietary readiness to change FV and Fat intake will be measured, respectively, by the Rhode Island Cancer Prevention Research Center's (1995) [35] Stage of Change for 5-A-Day and Stage of Change for Dietary Fat scales. Self-Efficacy to Increase Fruits and Vegetables and Decrease Saturated Fat [36] will also be measured, as will Self-Efficacy to Increase Exercise and Decrease Sedentary Behavior [37].

Changes in the attentional salience of healthy and unhealthy foods and activities will be measured by the Stroop Task given prior to both recreational laboratory sessions. The Stroop color-naming test quantifies the degree of interference produced by responding to words associated with high-fat foods, FVs, sedentary activity, and physical activity, as compared to neutral furniture words. A semantic category's ability to capture attention and produce response slowing or errors reflects its motivational salience. For example, attentional bias to food-related Stroop cards has been associated with food deprivation [38], intentional dietary restriction [39,40], and food craving [39].

The behavioral economic Want Task will be administered next at both laboratory sessions to measure the relative reinforcing value of healthy and unhealthy foods and activities. On each of the Want Task's 40 trials, participant will be given $4 to allocate across 15 g portions of food and 1 minute portions of activity. The relative price per unit of each commodity will vary: $0.25, $0.50, $1, $2, and $4. Participants will be advised to spend all of the money they are given, since none can be saved or taken home. Data will be scored to yield the following four outcome variables: 1) amount *purchased *of healthy/unhealthy commodities, 2) amount *consumed *of healthy/unhealthy commodities, 3) own-price elasticity/inelasticity (the degree to which participants' consumption of a good is influenced by price change for that good), and 4) cross-price elasticity/inelasticity (the degree to which participants' consumption of a good is influenced by price change for another good, resulting from substitution or complementarity).

Throughout the baseline and prescription phases participants will also report their mood and hunger. Daily, just after completing the end-of-day activity log, they will rate their hunger on a 1-10 scale and describe their mood using the Positive and Negative Affect Schedule (*PANAS*) [41].

### Primary Outcome Measures

#### Dietary Assessment

Saturated fat and FV consumption will be measured via daily PDA intake recordings. The saturated fat gram goal for those prescribed to decrease Fat intake will be determined by using the Harris-Benedict equation [42] to estimate number of calories needed to maintain weight. The saturated fat percentage then will be calculated using basal metabolic rate in order to prevent inflating the fat gram allowance due to superfluous calories (e.g. in beverages).

#### Activity Assessment

Physical activity will be measured by both accelerometry and self-report. For parallelism between the diet and activity outcomes, and between sedentary and physical activity assessments, the primary activity outcome will use self-report. During baseline, prescription, and follow-up periods, minutes of physical and sedentary activity will also be self-reported using an end-of-day 24-hour activity log in which participants account for every 15-minute time period of the day. To complete the log, participants will select activities from a modified version of the Compendium of Physical Activities [23], which defines moderate activity as any activity >3 METs. The Compendium will be altered for MBC by adding the four targeted sedentary leisure activities (i.e., television, movies, leisure computer, and video games). During baseline and prescription periods, minutes of moderate- and vigorous intensity physical activity also will be assessed directly using an accelerometer belted on the hip (Computer Science and Applications, Inc. Actigraph Model #7164).

#### Healthy Lifestyle Change

So that lifestyle behaviors are quantified on a common metric, we will generate z-scores reflecting each participant's average daily fruit/vegetable intake, saturated fat intake, daily physical activity, and daily targeted sedentary activity relative to the sample distribution at baseline. Z-scores will be standardized such that positive values indicate more healthful behavior change. Scores will be averaged across all four behaviors (FV, Fat, Sed, and PA) to derive a composite index that expresses the average healthy lifestyle change achieved by each participant.

### Analytic Plan

The primary analytic plan is designed to determine which behavioral prescription maximizes attainment of healthy lifestyle behavior change from baseline through prescription phase. The secondary analytic plan is to learn which prescription favorably influences behavioral and psychological processes, i.e., by fostering healthy substitutive or complementary change in lifestyle behaviors, fostering increased elasticity of unhealthy choices and increased inelasticity of healthy choices on the Want Task, and fostering increased self-efficacy, attentional bias, craving, and positive mood in association with healthy choices. The tertiary, exploratory, analytic plan is to examine maintenance of healthy lifestyle change. Distributions of all dependent variables will first be examined to search for outliers and to assess normality, with transformations undertaken as appropriate.

Outcomes will be evaluated within the context of three competing alternative hypotheses. The *familiarity hypothesis *posits that healthy simultaneous change in eating and activity will be maximized by the customary prescription to decrease intake of saturated fat and increase physical activity. The rationale is that this prescription reflects usual dieting and exercise practices, with which most adults have prior experience. The *behavioral economic *(optimal substitution-complementarity) *hypothesis *posits that healthy simultaneous change in eating and activity will be maximized when the prescription is to increase FVs while decreasing recreational screen time. The *low **inhibitory demand hypothesis *posits that healthy simultaneous change in eating and activity will be maximized when the prescription requires no inhibition/suppression of any rewarding eating or activity behaviors. This hypothesis predicts that the prescription to increase FV and PA will most improve healthy lifestyle behaviors because it requires no inhibitory self-control over high-rate, pleasurable eating and activity behaviors.

#### Primary Aim - Healthy Lifestyle

The first aim is to test our three alternative hypotheses about the optimum way to advise people to make two healthy behavior changes simultaneously, one in eating and one in activity. For this, we will use a linear mixed model (LMM) for longitudinal data [43] treating the composite health lifestyle z-score as the dependent variable, and including prescription condition as a between subjects factor and time as a within-subjects factor. The hypotheses predict a condition × time interaction, indicating that some conditions are more effective than others at bringing about healthy behavior change. If the overall omnibus F test of the condition × time interaction is significant, three planned comparisons will be performed to test the three competing hypotheses following procedures recommended by Rosenthal, Roscoe, and Rubin (2000) [44]. These comparisons will contrast the groups based on change over time for the composite healthy lifestyle z-score. Additionally, if the condition × time interaction is significant for the composite z-score, we will follow-up the overall test with separate tests of the interaction effect on each health behavior.

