## Methods/Design

### Study Design

The research design is a four by three factorial involving one between subjects factor (condition) with four levels and one within subjects factor (time) with three levels (baseline, prescription, follow-up). Inactive adults with suboptimal diet (N = 200) will be randomly assigned to one of four treatment conditions: a) ↑FV↑PA increase fruit and vegetable consumption to >5/day and increase moderate-vigorous physical activity to >60 minutes/day); b) ↓Fat ↓Sed: decrease saturated fat consumption to < 8% per day and decrease targeted sedentary leisure activity to < 90 minutes/day); c) ↑FV↓Sed: increase FV consumption to > 5/day and decrease Sed to < 90 min/day); or d) ↓Fat↑PA decrease saturated fat to < 8%/day and increase PA to > 60 min/day). The four intervention conditions represent a complete crossing of approach and avoidance oriented goals related to diet (↑FV or ↓Fat) and activity (↑PA or ↓Sed).

Participants will be studied through three study phases: a) usual behavior baseline (2 weeks); b) prescription phase (3 weeks) during which participants' payment will be contingent upon meeting pre-specified behavior change standards; and c) follow-up phase (4.5 months) during which payment will be contingent upon behavioral recording only. The protocol timeline is shown in Figure 3.

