#### PDA Tool

The PDA will be pre-loaded with a version of CyberSoft's Nutribase as well as a modified Compendium of Physical Activities [23] and software designed for the study. Cybersoft's nutrient database contains nutrient data for more than 30,000 foods. The Physical Activity Compendium has been expanded to include additional sedentary activities. A user-friendly interface enables participants to: a) click drop-down menus to enter foods and activities, b) conduct text searches for foods and activities, c) link entries to convey items eaten together as a combined food (e.g., sandwich combining bread, tomato, bacon, lettuce, mayonnaise), and d) enter and store custom foods. The software date- and time-stamps participants' entries and displays them to the coach in an organized format on the study server. Participants are instructed to enter foods immediately after eating them. Food entry prompts a "pop-up" question that, depending upon study condition, inquires about minutes of physical and/or targeted sedentary behavior since the last eating episode.

Coaches will provide corrective feedback when implausible reports suggest inaccurate or untimely reporting. Enrollees whose PDA and accelerometer data indicate that they display all four behavioral risk factors throughout the baseline period will be randomized. (This selection policy retains only high risk cases whose behavioral morbidities fail to remit spontaneously.) Participant allocation to condition will be concealed until the start of prescription period, when the project statistician determines the random assignment. Randomization, stratified by gender, will be performed using a computer generated sequence and the method of randomly permuted blocks.

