### Sample Size and Power

The effect size calculations assume a two-sided alpha set at .05 and were estimated for a power of .85.

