#### Primary Aim: Healthy Lifestyle

The outcomes for the primary aim are the z-scores for fruit and vegetables (FV), saturated fat (Fat), physical activity (PA) and sedentary activity (Sed) separately and averaged to form the composite healthy lifestyle score. Using pilot data to compare any one treatment condition to the other three, we found average effect sizes equal to .66, .63, .21 and .47 for change in FV, PA, Sed, and Fat, respectively. Therefore, we anticipate that we will have effect sizes approximately equal to .5 for the three comparisons on each outcome variable. Given an effect size of .5, a total of 200 participants, 50 per group, will yield adequate power for testing the three contrasts.

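### The primary model compares the arms on raw change in the composite; adjusting for the baseline composite (and for gender, the stratifier) would be at least as precise, at almost no cost

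*Protocol article*

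**What the plan says.** All references are to the protocol article.

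- **Primary Aim - Healthy Lifestyle (Analytic Plan).** The dependent variable is the composite z-score. The mixed model is described as "including prescription condition as a between subjects factor and time as a within-subjects factor". The planned comparisons are fixed on change: "These comparisons will contrast the groups based on change over time for the composite healthy lifestyle z-score". They are run only if the omnibus condition × time test is significant. The single-behaviour tests follow the same interaction.
- **Study Design.** Baseline is a level of the repeated factor: "one within subjects factor (time) with three levels (baseline, prescription, follow-up".
- **Healthy Lifestyle Change.** Each behaviour is scaled "relative to the sample distribution at baseline" and the four scores are averaged.
- **PDA Tool.** "Randomization, stratified by gender, will be performed using a computer generated sequence and the method of randomly permuted blocks". Gender is not named in any part of the Analytic Plan.
- **Sample Size and Power.** "The effect size calculations assume a two-sided alpha set at .05 and were estimated for a power of .85". The pilot inputs are effect sizes for change, and the planning value is about .5 for each comparison of one condition with the other three.

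**The concern.** Every participant records two weeks of baseline before randomisation, so the baseline composite is available for everyone at no extra cost. Randomisation makes the true arm means equal at baseline. A model that estimates a separate baseline mean in each arm and then subtracts it ignores this, and it carries the full baseline noise into the contrast. Adjustment removes only the part of the baseline that predicts the outcome.

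The stratifier raises a similar issue. Stratifying by gender balances it across arms. If gender predicts change and the model omits it, its variance stays in the residual although it no longer contributes to the sampling error of the arm comparison.

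What is at stake is precision in the primary test, and slight conservatism if gender matters. Bias and false-positive risk are not at stake.

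**Working it through.** **1. The plan's own figure.** Inputs from Sample Size and Power: effect size d = .5, 50 per group, two-sided alpha .05. One condition against the other three is 50 versus 150.

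Noncentrality = .5 / √(1/50 + 1/150) = .5 / .1633 = 3.06. With 196 degrees of freedom the power is .86, against the stated .85. The figure reproduces.

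**2. What the mixed model estimates.** With two time points, complete data and a free baseline mean per arm, the condition × time contrast should equal the difference in mean change. A simulated data set of 200 confirmed it. The mixed model and the change-score analysis both gave .663 with standard error (SE) .170. Regression of the outcome on arm and baseline gave SE .153.

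**3. Variance with and without baseline adjustment.** Let s0 and s1 be the composite SDs at baseline and prescription, and ρ their correlation.

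- Change: s0² + s1² − 2ρ·s0·s1
- Baseline-adjusted: s1²(1 − ρ²)
- Difference: (s0 − ρ·s1)², which is never negative
- Ratio at s0 = s1: (1 + ρ)/2

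The article gives neither ρ nor s1/s0, so both are assumed over a range. Power is for d = .5 on the change scale, one arm versus three.

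| s1/s0 | ρ | Change variance | Adjusted variance | Ratio | Power |
|---|---|---|---|---|---|
| 1 | .3 | 1.40 | 0.91 | .65 | .97 |
| 1 | .5 | 1.00 | 0.75 | .75 | .94 |
| 1 | .7 | 0.60 | 0.51 | .85 | .91 |
| 1.5 | .3 | 2.35 | 2.05 | .87 | .90 |
| 1.5 | .5 | 1.75 | 1.69 | .96 | .87 |
| 1.5 | .7 | 1.15 | 1.15 | .998 | .86 |
| 2 | .3 | 3.80 | 3.64 | .96 | .88 |
| 2 | .5 | 3.00 | 3.00 | 1.00 | .86 |
| 2 | .7 | 2.20 | 2.04 | .93 | .89 |

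**4. Gender.** A gender main effect cancels from a change contrast: in the simulated data the SE was .1698 with and without it. Only an effect of gender on change matters. If gender explains a share R² of the variance of change (assumed), the unadjusted SE is too large by a factor 1/√(1 − R²).

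- R² = .05: 1/√.95 = 1.026. Power after adjustment is .88.
- R² = .10: 1/√.90 = 1.054. Power after adjustment is about .89.

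In 4,000 simulated stratified trials per setting, the unadjusted test had type I error .047 for a gender effect on change of 0.3 SD and .044 for 0.6 SD. The error is conservative.

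**5. The omnibus gate.** One arm differing by .5 SD from three equal arms has deviations .375 and −.125 (three times) from the grand mean. The noncentrality is 50 × (.375² + 3 × .125²) = 9.375, and the F(3,196) test has power .72. Dividing 9.375 by the ratios above gives .90, .85 and .80 at equal SDs for ρ = .3, .5 and .7. At s1/s0 = 1.5 it gives .72 to .79.

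**The case against.** A condition × time mixed model is a standard analysis and is unbiased under randomisation. Here it fits an outcome defined as change and a sample size built on effect sizes for change: "we found average effect sizes equal to .66, .63, .21 and .47 for change in FV, PA, Sed, and Fat, respectively". Nothing in that chain is contradictory, and this stands.

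The larger gains assume equal SDs, and the design suggests otherwise. Entry requires all four risk behaviours, and they must persist through baseline recording. The baseline range is therefore cut off at the thresholds, after which participants are moved past them. A larger prescription-phase SD is plausible, and the gain may then be close to zero. This also stands, and it is why the lower range is given equal weight.

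A condensed article may leave covariates, including the stratifier, to the full protocol or analysis plan, and no passage excludes them. This weakens the gender part. It does not remove the baseline part, which rests on stated model terms and a stated contrast on change.

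Two stronger readings are tempting, and the article supports neither:

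- **That the change comparison misstates its standard error.** The SE is correct for its own estimator, only usually larger than necessary. Overstatement arises solely from omitting gender, solely if gender predicts change, and it is small.
- **That the one-versus-three contrasts are short of power.** Taken alone they have .86 against a planned .85. Only the omnibus gate lowers the figure, and that is a separate feature of the testing sequence.

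**Conclusion.** The point holds as a precision recommendation. As written, the primary contrast is a raw-change comparison, and adjusting for the baseline composite cannot do worse beyond about one degree of freedom.

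The reduction in variance is about 15-35% at equal SDs with correlation .7 down to .3, and 0-13% if the prescription-phase SD is 1.5 to 2 times the baseline SD over the same correlations. Power for the ungated contrast moves from .86 to between .91 and .97 in the first case, and to between .86 and .90 in the second.

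The gender part is smaller and conditional: an SE about 3-5% too large if gender explains 5-10% of change variance, and no loss if it explains none. The correlation, the SD ratio and the gender share are all assumptions. The equivalence with raw change assumes complete data.

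**What to change.** State in the Primary Aim analysis that one of these two forms will be used:

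- the mixed model with the four arm means constrained to be equal at baseline, plus gender and gender × time; or
- a model of the prescription-phase composite with arm, the baseline composite and gender as covariates.

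In the mixed model a gender main effect alone would not sharpen the change contrast, so the interaction with time is needed. Use the same form for the four single-behaviour models, each with its own baseline value.

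The cost is a sentence or two in the analysis plan and one or two degrees of freedom. Both variables are already collected. The planned contrasts keep their meaning, because under randomisation the adjusted comparison targets the same between-arm difference. Fixing the form before the data are analysed also rules out choosing covariates afterwards.

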The coach will activate two feedback and decision support thermometers on the participant's PDA - one for diet and one for activity. Depending on participant's assigned condition, the diet thermometer will display either what percent of the day's FV intake goal has been attained thus far or how much of the day's saturated fat gram allowance has been used. Similarly, the activity thermometer will display either how much of the day's physical activity goal has been attained thus far or how much of the day's targeted recreational sedentary activity allowance has been used. For prescription week 1, goals will be set at the half-way point: a level of attainment that is midway between the individual's baseline diet and activity levels and the prescribed target levels. Goals and goal thermometers will be re-set for prescription weeks 2 and 3 to the full target goal standard. Participants will continue to upload data daily during all three weeks of the prescription phase. They will communicate with their coaches via telephone or e-mail to problem-solve challenges with attainment of behavioral targets. The coach will also help participants troubleshoot any difficulties with study equipment and will, as needed, call in technical support.

Consistent with 5-A-Day Program Guidelines [24], the PDA program assigns participants no credit for FVs that have a high calorie content (e.g., avocados, coconuts, olives). FVs with added fat and sodium will also be excluded if more than 30% of calories are from fat, more than 10% of calories are from saturated fat, or more than 480 milligrams of sodium have been added. FVs that are processed by drying, freezing, or canning will be included, as will any juice that is 100% juice or juice concentrate. A serving will be defined by USDA [25] guidelines as: a medium piece of fruit; half a cup of raw, cooked, canned, or frozen FVs; one cup of leafy salad greens; one quarter cup of dried fruit; six ounces (three-quarters cup) of 100% fruit or vegetable juice; or a half cup of cooked or canned beans, peas, or legumes (e.g., lentils, black beans).

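### The stated power of .85 belongs to ungated contrasts; behind the omnibus gate it can be as low as about .71, and the plan leaves open which time levels the gate uses

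*Protocol article*

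**What the plan says.** The Protocol article treats the primary test in three places.

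- **Analysis** (Primary Aim - Healthy Lifestyle, under Analytic Plan). A linear mixed model is fitted to the composite z-score, with condition and time as factors. The contrasts are conditional: "If the overall omnibus F test of the condition × time interaction is significant, three planned comparisons will be performed". The text states no multiplicity adjustment for the three contrasts and refers to a cited source for the contrast procedures.
- **Power** (Sample Size and Power). The calculations "assume a two-sided alpha set at .05 and were estimated for a power of .85". Pilot effect sizes come from comparing one condition with the other three, and the section concludes: "Given an effect size of .5, a total of 200 participants, 50 per group, will yield adequate power for testing the three contrasts". The omnibus test is not mentioned.
- **Time** (Study Design). The design has "one within subjects factor (time) with three levels (baseline, prescription, follow-up"). The Analytic Plan puts the primary question more narrowly, as which prescription "maximizes attainment of healthy lifestyle behavior change from baseline through prescription phase", and makes maintenance a tertiary, exploratory aim with its own model. The primary-aim paragraph refers to time without listing its levels.

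**The concern.** The sample size is justified for one procedure and the primary analysis is another. A contrast behind a gate succeeds only if the gate and the contrast are both significant, so its power cannot exceed that of the contrast alone and may be well below it. A real .5 SD advantage for one prescription could go untested because the omnibus test missed.

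The time levels matter for the same reason. With baseline and prescription only, the interaction has 3 × 1 = 3 df. With follow-up included it has 3 × 2 = 6 df. The gate for a baseline-to-prescription question would then depend partly on what happens in a phase that the plan treats as exploratory.

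**Working it through.** **Inputs from the Protocol article:** two-sided alpha .05; target power .85; effect size .5 for one condition versus the other three; 50 per group, 200 in total; contrasts run only after a significant omnibus interaction.

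**Assumptions, because the article does not fix them:** the effect size is in SD units of the baseline-to-prescription change (SD = 1); equal variances; 196 error df; no dropout; no adjustment of the contrasts after the gate.

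**1. The plan's own figure.** SE = √(1/50 + 1/150) = .1633. Noncentrality = .5/.1633 = 3.06. Power is .865 by the normal approximation and .861 by the noncentral t with 196 df. This matches .85 closely (48 per group would be enough), so the stated power is that of the ungated contrast.

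**2. The gate at 3 df, one condition better and three equal.** The means (.5, 0, 0, 0) have grand mean .125. Noncentrality λ = 50 × [.375² + 3 × .125²] = 50 × .1875 = 9.375. Power of F(3, 196) is .721. The probability that the gate and the contrast are both significant is .712 (simulation, 1,000,000 runs). For a contrast of .5 this is the lowest value at 3 df, because any spread among the other three arms adds to λ.

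**3. Other patterns, target contrast held at .5, 3 df.**

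| Pattern of means | λ | Gate | Gate and contrast | Holm, no gate |
|---|---|---|---|---|
| Other three equal | 9.375 | .721 | .712 | .745 |
| Others spread ±.1 | 10.375 | .769 | .747 | .744-.752 |
| Others spread ±.2 | 13.375 | .874 | .812 | .745-.770 |
| Others spread ±.3 | 18.375 | .959 | .851 | .754-.800 |
| Two high, two low (±.375) | 28.125 | .997 | .861 | .816-.829 |
| Three at .375, one at -1.125 | 84.375 | >.999 | .862 | .843-.853 |

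The Holm ranges cover the choice of which two other arms supply the remaining contrasts.

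**4. The gate at 6 df.** Under compound symmetry with a change-score SD of 1, the within-person error variance is .5. With a time profile (0, 1, c) for the better arm, λ = 50 × .1875 × SS/.5, where SS is the sum of squares of the profile about its mean.

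- Effect half maintained (c = .5): SS = .5, λ = 9.375, power of F(6, 392) = .60.
- Effect fully kept (c = 1) or fully lost (c = 0): SS = 2/3, λ = 12.5, power = .75.

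These values are for the gate alone.

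**5. Family-wise error with the gate at 3 df, contrasts each at .05.** Under the global null it is .043. With two null contrasts and the other two arms at ±.3 it is about .089; at ±.5 and beyond it is about .094-.095.

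**The case against.** The strongest reply is that the fall to about .71 depends on a pattern of means that the article does not state. It expects about .5 for all three comparisons. Taken literally, that means three tied arms with the fourth 1.5 SD lower or, if only absolute size counts, two high and two low. In both cases the gate costs nothing and power is .86. This stands in part: .71 is a floor at 3 df, not a property of the plan. But neither pattern has a single best arm, whereas the three hypotheses compete and each names one arm as best. One better arm among similar ones is the natural case when one hypothesis is true.

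Protected testing is also a recognised choice. The article says that its hypotheses predict an interaction, and the same gate governs the follow-up tests of the single behaviors. This stands, and it is why keeping the gate is acceptable.

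Three stronger readings are tempting but not supported:

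- **That the gate is a 6-df test.** This is one reading. The three levels describe the overall design, and the primary-aim paragraph does not say that follow-up enters the primary model. What stands is the ambiguity.
- **That a promise of strong error control is broken.** The article makes no such claim, and the cited contrast procedures or an analysis plan may add an adjustment.
- **That week 1 dilutes the primary effect.** It is true that "For prescription week 1, goals will be set at the half-way point". But nothing says that the primary model averages week 1 with weeks 2-3, the maintenance model separates them, and the article does not say which weeks the pilot effects cover. No loss of power can be derived from this.

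**Conclusion.** The point holds in a conditional form. The stated .85 is sound for the ungated contrast but is not the power of the primary procedure as written. At d = .5 and 50 per group, gated power lies between about .71 (one arm better, the other three equal) and .86 (other arms widely separated), given a 3-df interaction. In the single-winner case the gate costs about 15 points (.861 - .712 = .149). With three time levels, the gate alone has power of about .60 to .75, assuming compound symmetry and that between half and all of the effect is kept, or that all of it is lost. The article leaves open which gate applies.

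Family-wise error is held near .04 under the global null, but can reach about .094 when two contrasts are null, if no further adjustment is made. A reader should not infer that power is .72 whatever the means, or that removing the gate would always help.

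**What to change.** 1. State that the primary interaction and the three contrasts use baseline versus prescription only, and that follow-up belongs to the exploratory maintenance model. This settles the 3-df versus 6-df question and stops follow-up differences from opening the primary contrasts.
2. Restate power for the gated procedure: about .71 if one arm is .5 better and the others are equal, rising to about .86 as the other arms differ, with the assumed pattern of means given.
3. Say that the gate protects the family-wise error only under the global null, unless an adjustment of the contrasts is added.

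Option, not a required change: test the three contrasts directly with Holm at an overall two-sided .05. Power is about .75 in the equal-others case and family-wise error is controlled strongly. The price is lower power than the gated procedure once the other arms differ by about ±.2 or more (.745-.770 against .812), and a separate rule would be needed for the single-behavior tests that the gate now governs. Removing the gate with no adjustment is not an alternative: family-wise error under the global null would be about .13.

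Items 1 to 3 need only wording and a restated power figure, with no added participants or data. The cost is a less favorable stated power. For scale, omnibus power of .85 in the equal-others case would take about 67 per group (268 in total).
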